### Participating surgeons

We have selected three experienced pancreatic surgeons and several nurses on our medical and research team available to perform surgeries and postoperative care for enrolled patients. The clinician performing the operations will be required to have an associate senior or senior title and have completed at least 30 laparoscopic or open pancreatic necrotic tissue drainage or debridement procedures, indicating their capacity to handle emergencies during the operation and ensure the treatment quality for enrolled patients.

### Primary outcome

The primary outcome is the composite endpoint, which consists of mortality and severe complications (Clavien-Dindo ≥ IIIa). According to the Clavien-Dindo classification, postoperative complications classified as higher than Grade IIIa will be regarded as clinically significant (Table 1) [9].

**Table 1 Tab1:** Clavien-Dindo Classification

Grade	Definition
I	Any complication that deviates from the natural course after surgery, including the use of antiemetics, antipyretics, analgesics, diuretics, infusion, and physical therapy, as well as bedside debridement of incision infection
II	Medications other than those permitted for grade I complications are required, including blood transfusion and total parenteral nutrition support
*III*	Surgical, endoscopic, and radiotherapy are required
IIIa	No general anesthesia is required
IIIb	Need for general anesthesia
*IV*	Life-threatening complication, including centeral nervous system complications and required intermittent monitoring or intensive care unit (ICU) treatment
IVa	Single organ dysfunction
IVb	Multi-organ dysfunction
V	Death

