#### Retroperitoneal surgical approach

(1) Incision selection: Carefully evaluation will be made of the results of the CT scan before surgery, and the midaxillary line is usually used as the body surface marker. The incision should be selected near the midaxillary line closest to the abscess (surgery can be performed through the left or right midaxillary line) while avoiding the ascending colon, duodenum, and descending colon as much as possible. The incision length is usually approximately 5 cm. (2) The retroperitoneal passage will be established: Incise the skin, subcutaneous tissue, and abdominal wall muscle, and hemostasis of the abdominal wall muscle should be thorough to avoid postoperative wound bleeding. After entering the peritoneum through the retrocolic space, the abscess cavity will be determined by fine-needle puncture and then bluntly separated into the abscess cavity. Video-assisted pancreatic necrotic tissue debridement and drainage tube placement are the same as those in the omentum sac surgical approach. Surgery can be performed through the left and right midaxillary line or bilateral approaches. The first operation is usually performed under general anesthesia with tracheal intubation or laryngeal mask, and the second operation may be performed under local anesthesia depending on the abscess and the general condition.

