### “Step-up” minimally invasive pancreatic necrotic tissue debridement

“Step-up” minimally invasive pancreatic necrotic tissue debridement which uses PCD as the initial treatment option for IPN. The retroperitoneal approach is the preferred approach for PCD treatment under the guidance of B-ultrasound or abdominal CT scans. “Step-up” minimally invasive surgery should be considered if the patient’s infection symptoms do not resolve within 48 h following PCD treatment. The surgical approach is the same as the “One-step,” and the surgical approach was retroperitoneal or omentum sac, depending upon the path of the PCD drainage tube and preoperative imaging examination. If there is residual infection in the abdominal cavity after minimally invasive surgery, PCD treatment is preferred. Open surgery is only used as the last rescue measure after the failure of minimally invasive surgery.

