### Perioperative treatment for enrolled patients

For patients who received “One-step” minimally invasive pancreatic necrotic tissue debridement, clinicians must provide symptom-based treatment, such as electrocardiograph monitoring, antibiotics, proton pump inhibitors, analgesics, octreotide, and nutrition support. Routine blood tests, serum CRP, PCT, IL-6, and arterial blood gas tests will be used to monitor delayed bleeding, incision, and/or abdominal infection after surgery. After the recovery of gastrointestinal function, a semi-liquid diet can be gradually administered until a normal diet is resumed. In addition, it is also necessary to pay attention to the characteristics of the drainage fluid in the abdominal drainage tube and be alert to delayed abdominal hemorrhage. When the amount of drainage fluid in the abdominal drainage tube is gradually reduced and the characteristics of the drainage fluid are clear, the drainage tube can be removed gradually. The patients can then be discharged from the hospital.

For patients who received “Step-up” minimally invasive pancreatic necrotic tissue debridement, clinicians provide electrocardiograph monitoring, antibiotics, proton pump inhibitors, analgesics, octreotide, and nutrition support after receiving PCD therapy. Routine blood tests, serum CRP, PCT, IL-6, and arterial blood gas tests are continued to monitor the abdominal infection. If the patient’s infection symptoms are resolved, the current therapies will be continued until normal status is achieved. If the patient’s infection symptoms are not relieved within 48 h of PCD treatment, they will undergo minimally invasive pancreatic necrotic tissue debridement. The postoperative treatment is the same as the “One-step” approach.

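### The primary composite is stated at two different Clavien-Dindo cuts, and its grading table does not say whether the Step-up arm's planned move from drainage to debridement is a graded event

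*Protocol article*

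**What the plan says.** The protocol article's Primary outcome section defines the endpoint as "mortality and severe complications (Clavien-Dindo ≥ IIIa") and adds in the next sentence that "postoperative complications classified as higher than Grade IIIa will be regarded as clinically significant".

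Table 1 in the same section describes grade III as "Surgical, endoscopic, and radiotherapy are required". It divides the grade by anaesthesia: IIIa without general anaesthesia, IIIb with it. The table's grade I entry begins "Any complication that deviates from the natural course after surgery".

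The treatment sections contain three procedures that bear on these grades:

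- **Planned escalation in Step-up.** Drainage (PCD) comes first. If infection symptoms persist at 48 h, Perioperative treatment for enrolled patients says "they will undergo minimally invasive pancreatic necrotic tissue debridement". The Step-up section describes surgery at the same point only as something to consider.
- **Anaesthesia.** Retroperitoneal surgical approach says "The first operation is usually performed under general anesthesia with tracheal intubation or laryngeal mask", and that a second operation may be done under local anaesthesia.
- **Residual infection.** The Step-up section says "If there is residual infection in the abdominal cavity after minimally invasive surgery, PCD treatment is preferred".

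Secondary outcome lists the number of procedures, PCD included, as a separate outcome. Sample size assumes composite rates of about 20% (One-step) and 45% (Step-up), with a one-sided 0.05 test, 80% power, 20% withdrawal and 64 patients per group.

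**The concern.** There are two separate problems in the definition of the primary endpoint.

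First, the two sentences disagree on grade IIIa. This grade is likely to be populated here: re-drainage without general anaesthesia and a second operation under local anaesthesia would both be IIIa if graded. The table makes this harder to settle, because its grade III entry names a treatment that the trial does not use and leaves out image-guided drainage, which is central to it.

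Second, grade III is reached by needing a procedure. In Step-up, debridement after unsuccessful drainage is part of the assigned strategy. If an assessor graded it, it would usually be IIIb and would count under either cut. In One-step the same operation is the index treatment and would not be graded. Nothing shown tells the assessor to leave the planned step out.

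At stake are which events enter the primary analysis and, if escalation were scored, whether an advantage for One-step could appear with no difference in harm.

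**Working it through.** **1. The plan's own sample size.** Inputs from Sample size: 45% and 20%, one-sided 0.05, 80% power, 20% withdrawal, 1:1.

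- Pooled formula: mean rate 0.325; √(2 × 0.325 × 0.675) = 0.6624; √(0.45 × 0.55 + 0.20 × 0.80) = 0.6384.
- n = (1.645 × 0.6624 + 0.842 × 0.6384)² / 0.25² ≈ 42.3.
- With continuity correction: (42.3/4) × [1 + √(1 + 4/(42.3 × 0.25))]² ≈ 50.02, so 51 per arm.
- Withdrawal: 51/0.80 = 63.75, so 64 per arm and 128 in total.

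The stated 128 is reproduced. The arithmetic is not at fault, and 51 evaluable per arm is the planned analysis size.

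**2. The two cuts side by side.**

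| Event, if graded | Grade | IIIa or above | Above IIIa |
|---|---|---|---|
| Drainage for residual infection, no general anaesthesia | IIIa | counts | does not count |
| Second operation, local anaesthesia | IIIa | counts | does not count |
| Debridement, general anaesthesia | IIIb | counts | counts |

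**3. If planned escalation were scored.** Assumptions, none of them in the document: the same true rate h = 20% in both arms, and a share s of otherwise event-free Step-up patients scored only because of the planned step.

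- Observed Step-up rate = h + (1 − h)s.
- Probability of a significant result = Φ[(d − 1.645 × SE0)/SE1], where d is the observed difference, SE0 the pooled and SE1 the unpooled standard error; 51 per arm, no continuity correction.
- Example, s = 30%: rate 0.20 + 0.80 × 0.30 = 0.44; d = 0.24; SE0 = √(0.32 × 0.68 × 2/51) = 0.0924; SE1 = √((0.2464 + 0.16)/51) = 0.0893; (0.24 − 0.1520)/0.0893 = 0.986; Φ = 84%.

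| s | Step-up reads | Superiority shown with no difference in harm |
|---|---|---|
| 10% | 28% | 24% |
| 20% | 36% | 56% |
| 30% | 44% | 84% |
| 40% | 52% | 97% |

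A share of 0.25/0.80 = 31% would by itself turn 20% into the planned 45%. With h = 45% instead, the probabilities for s = 10%, 20%, 30% and 40% are 14%, 30%, 51% and 73%. A two-sided 0.05 test with all 64 per arm gives 52%, 84% and 97% for s = 20%, 30% and 40% at h = 20%.

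**4. If IIIa were dropped.** Assume that a share f of events in each arm is IIIa only and that 20% and 45% were set with IIIa included.

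- For f = 1/3 the rates become 0.45 × 2/3 = 30% and 0.20 × 2/3 = 13.3%. Then d = 0.1667, SE0 = 0.0816, SE1 = 0.0799, and (0.1667 − 0.1342)/0.0799 = 0.41, so power is about 66%.
- With f = 0, the same formula gives 86% (above 80% because it has no continuity correction).
- For f = 10%, 20%, 30% and 50%, power is 81%, 75%, 68% and 53%.
- Two-sided at 64 per arm, f = 1/3 takes power from 86% to about 63%.

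**The case against.** The strongest objection is that the document never says the planned step is counted. A reader might infer from Table 1 that it is, and that the endpoint therefore measures allocation. The text does not support that. It grades postoperative complications, the table opens with departures from the expected course, and the number of procedures is kept as a separate secondary outcome. On an ordinary reading, planned debridement is not a complication. This stands: the risk is conditional on how assessors grade, and the document does not fix it either way.

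The asymmetry is also incomplete. Repeat procedures in One-step could be graded too, and the table in step 3 inflates only Step-up. That stands for repeat procedures, though not for the first debridement, which is the index treatment in only one arm.

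The escalation and IIIa-only shares are assumptions. The planning rates may already include escalation, or may rest on either cut; the document does not say. A reader might take the near match of 44% with 45% as evidence that escalation explains the planned difference. It is not evidence, because the 30% was chosen.

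Scoring rules may sit in the SOPs or CRF, which are not shown, so the lack of a detailed rule is not itself an error. This does not answer the contradiction between the two printed sentences or the grade III entry. The second sentence speaks of clinical significance and may be a slip, but it directly follows the endpoint definition and disagrees with it.

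**Conclusion.** The contradiction on grade IIIa is certain and sits in the primary endpoint, so it must be corrected. The grade III entry is worded wrongly for this trial, which is minor alone but adds to the uncertainty about drainage.

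The escalation point holds as a conditional risk: grade III depends on needing a procedure, and nothing shown excludes the Step-up arm's planned debridement. Under the stated assumptions (20% true rate in both arms, escalation scored in Step-up only), 10% to 40% scored escalation gives false superiority about 24% to 97% of the time at 51 per arm, one-sided 0.05. Losing one third of events as IIIa only would take power from 86% to about 66%. These are ranges on inputs that the document does not supply, not estimates of what will happen. The sample size of 128 is correctly computed from its stated inputs.

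**What to change.** 1. Use grade IIIa or higher in both sentences of Primary outcome, in line with the stated endpoint definition.
2. In Table 1, replace radiotherapy in the grade III entry with radiological (image-guided) intervention.
3. State, in the same words for both arms, that the protocol-defined step from PCD to debridement is not by itself a complication.
4. State once how repeat drainage or debridement for residual infection is graded, and apply it equally to both arms. Do not remove these procedures from the endpoint by default: they may reflect failed control of infection, and excluding them would be a debatable change of endpoint.
5. State in Sample size whether the 20% and 45% were derived on this basis, and restate the power if they were not.
6. Reconcile the Step-up section with Perioperative treatment for enrolled patients on whether debridement after persisting symptoms is to be considered or is to follow, since this determines which escalations are planned.

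The text changes are small: endpoint wording, one table entry and a grading note for the CRF. The trial began in May 2021 and surgeons know the allocation, so the rule should be dated and applied uniformly to patients already enrolled. The real cost is that the expected Step-up rate may prove lower than 45%, which would make the stated power less favourable.

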### Secondary outcome

The incidence of organ dysfunction and organ function were evaluated according to the modified Marshall score.Complication: The complication rate mainly includes short-term and long-term complication rates, among which short-term complications include bleeding, gastrointestinal perforation, and pancreatic leakage. Long-term complications include incisional hernia, pancreatic endocrine and exocrine dysfunction, chronic pancreatitis, and portal hypertension. Pancreatic endocrine dysfunction was defined as HbA1c ≥ 6.5% (48 mmol/mol) and/or FPG ≥ 126 mg/dl (7.0 mmol/l) 3 months after diagnosis or pancreatitis. Pancreatic exocrine dysfunction was determined in a variety of ways including direct pancreatic function testing, measurement of fecal elastase or fecal fat levels (72 h fecal fat excretion > 7 g/d) and need for oral pancreatic enzyme replacement therapy. Chronic pancreatitis was defined as repeated upper abdominal pain; abnormal serum or urine pancreatic enzyme concentrations (lipase or amylase activity 2–3 times above the upper limit of normal); abnormal exocrine function (stool elastase < 200 µg/g) while the endosonography/CT/MRI imaging shows dilated main duct and side branches, intraductal and parenchymal calcifications[10, 11].The number of surgical procedures which includes PCD and the total number of operations.Mortality: The incidence of in-hospital death and deaths within 90 days of discharge.The length of hospital stays, the length of intensive care unit (ICU) stay, and hospitalization costs.Changes in inflammatory markers, including white blood cell (WBC), interleukin-6 (IL-6), C-reactive protein (CRP), and procalcitonin (PCT)

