#### Omentum sac surgical approach

(1) Incision selection: The preoperative CT scan will be carefully evaluated, and the boundary of the peripancreatic abscess will typically be marked by the xiphoid process or umbilicus. The incision should be selected in the midline nearest to the abscess, and the stomach and transverse colon should be avoided as far as possible. The incision length is usually approximately 5 cm. (2) Passage is established through the omental sac: After entering the abdominal cavity, the gastrocolic ligament is incised below the vascular arch of the gastroepiploic artery. Bleeding caused by injury to the gastroepiploic vessels must be thoroughly sutured to avoid postoperative bleeding in the abdominal cavity or the omental sac. The gastrocolic ligament and parietal peritoneum are sutured around the circumference to establish access and protect the abdominal cavity from pus inflow. The location of the abscess cavity will be determined by fine-needle puncture (application of intraoperative ultrasound positioning) and bluntly separate into the abscess cavity. (3) Video-assisted pancreatic necrotic tissue debridement: After the tissue is collected for bacterial culture, pus is absorbed as much as possible, and the abscess cavity is observed through video equipment. Under video guidance, the necrotic tissue is removed with an aspirator, oval forceps, or laparoscopic instrument, blood vessels are carefully protected, and immature necrotic tissues are preserved. (4) Place drainage tube: The drainage tube is placed under laparoscopy and the location and number of placements depend on the location and size of the abscess. It is recommended to use a 30–36Fr three-chamber drainage tube to reduce the risk of blockage.

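### The primary endpoint does not say whether the planned debridement after PCD in the Step-up arm counts as a grade III event; read literally, Table 1 lets it count in that arm only

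*Protocol article*

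**What the plan says.** All references are to the protocol article.

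- **Primary outcome.** The endpoint is a "composite endpoint, which consists of mortality and severe complications (Clavien-Dindo ≥ IIIa"). The next sentence says that "postoperative complications classified as higher than Grade IIIa will be regarded as clinically significant", so the two sentences disagree on whether IIIa itself counts. IIIb counts under both.
- **Table 1.** Grade III is defined by a need for surgical, endoscopic or radiological-type treatment. IIIa is without general anesthesia and IIIb is with it. The grade I row describes "Any complication that deviates from the natural course after surgery". No row mentions planned steps.
- **Step-up section and Perioperative treatment.** If infection symptoms are not relieved within 48 h of PCD, "they will undergo minimally invasive pancreatic necrotic tissue debridement".
- **Retroperitoneal surgical approach.** "The first operation is usually performed under general anesthesia"; a second operation may be under local anesthesia.
- **Status of PCD.** A secondary outcome is "The number of surgical procedures which includes PCD" and the total number of operations. The One-step section also calls PCD a surgical procedure.
- **Further steps.** In the Step-up section: "If there is residual infection in the abdominal cavity after minimally invasive surgery, PCD treatment is preferred". In the omentum sac technique, "immature necrotic tissues are preserved", and the retroperitoneal section foresees a second operation.
- **Blinding.** Patients are blinded; the surgeon knows the allocation.

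**The concern.** Clavien-Dindo grades a complication by what is done about it. That works when every patient has one index operation and any later procedure is unplanned. Here the control strategy is a sequence of procedures. If PCD is the first surgical procedure, infection that persists and leads to debridement under general anesthesia fits the IIIb row taken alone. In One-step the same debridement is the index procedure, so it can never be an event.

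If escalation is scored, the composite partly measures how often Step-up steps up. It then overlaps with the number-of-procedures outcome and is no longer a clean comparison of death and severe complications. If it is left to case-by-case judgement, that judgement may be made by staff who know the arm. Either way, the meaning of the primary result depends on a choice that the endpoint definition does not make.

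**Working it through.** **1. The plan's own figure.** Inputs from Sample size: 20% (One-step), 45% (Step-up), one-sided α 0.05, power 80%, withdrawal 20%.

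Pooled-variance formula, with mean rate 0.325 and difference 0.25:

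n = [1.645·√(2·0.325·0.675) + 0.842·√(0.20·0.80 + 0.45·0.55)]² / 0.25² = 42.3

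Continuity correction: (42.3/4)·[1 + √(1 + 4/(42.3·0.25))]² = 50.02, rounded up to 51 per arm.

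Withdrawal: 51/0.80 = 63.75, rounded up to 64 per arm, 128 in total. The stated sample size reproduces exactly and is not in question.

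**2. Model for the scoring question.** Let c be the true rate of death or severe complication, the same in both arms. Let f be the share of Step-up patients whose planned debridement is scored as an event, independently of c. Then:

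Step-up rate = c + (1 − c)·f; One-step rate = c

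The documents give no value for f, so a range is assumed. c = 20% is the plan's One-step figure.

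**3. Chance of declaring One-step superior**, by exact binomial enumeration of the pooled chi-square test, 51 per arm:

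| f | Step-up rate at c = 20% | One-sided 5% | Two-sided 5% |
|---|---|---|---|
| 0 | 20% | 5.1% | 2.5% |
| 10% | 0.20 + 0.80·0.10 = 28% | 25% | 16% |
| 20% | 0.20 + 0.80·0.20 = 36% | 57% | 44% |
| 31.25% | 0.20 + 0.80·0.3125 = 45% | 87% | 78% |
| 50% | 0.20 + 0.80·0.50 = 60% | 99.6% | 99% |

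**4. Sensitivity to c.** For c from 10% to 30% (one-sided, 51 per arm), the chance is 19–36% at f = 10%, 43–77% at f = 20% and 72–97% at f = 31%. With 64 per arm and c = 20% it is 28%, 65% and 93%.

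**5. If One-step re-interventions also score.** Suppose second operations in 20% of One-step patients are counted: the One-step rate is 0.20 + 0.80·0.20 = 36%. Against f = 50% in Step-up (60%), the chance falls from 99.6% to 78%. The bias shrinks but does not vanish in this example. It would vanish if the scored shares were equal in the two arms.

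**The case against.** The strongest reply is that the document already points to the sensible reading. The endpoint is limited to postoperative complications, and the grade I row requires deviation from the natural course. Debridement after PCD is the prescribed course, and the persisting infection is the disease under treatment. The short-term complications named under Secondary outcome are bleeding, perforation and pancreatic leakage, with procedures counted separately. Grading conventions may also sit in a full protocol or standard operating procedure that is not shown.

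Much of this stands. A reader might infer from the grade III rows that planned debridement is a IIIb event under this plan. The documents do not support that: counting it is one possible reading, and general anesthesia is only usual for the first operation. A debridement under local anesthesia would be IIIa, which counts under one of the two threshold sentences and not under the other.

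A reader might also infer, because f = 31.25% turns 20% into 45%, that the planned contrast consists of escalation. That value of f was solved from the 45%, and nothing shown says that the 45% includes planned debridement. Nor is the bias wholly one-sided, since One-step patients may also have second operations.

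What the reply does not do is close the question. The list of complications is not exhaustive. Relief and persistence of infection after PCD are both foreseen, so the natural-course wording does not settle which is a deviation. This is also more than omitted detail: the article prints the operative definition, and its rows, applied as written, treat the same operation differently in the two arms.

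**Conclusion.** The point holds as an unfixed, arm-asymmetric scoring rule in the primary endpoint. The text neither counts nor excludes protocol-directed debridement after PCD, and gives no start of grading. The sample size arithmetic is sound.

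The potential size is large: scoring planned debridement in as few as 10% of Step-up patients raises the one-sided error from 5% to about 25% when the true rate is 20% in both arms. This rests on an assumed escalation share, on every such step being scored, on independence from other events, and on no One-step re-intervention being scored. The figures are therefore an upper-end illustration of one reading, not a prediction of the trial's result. The matter should be settled before the endpoint is graded, because the interpretation of the primary result turns on it.

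**What to change.** Add to Primary outcome, in the same words for both arms:

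- when grading starts;
- that protocol-directed debridement after PCD does not by itself score grade III or higher, while a new event (for example bleeding, perforation, organ dysfunction or death) does;
- one common scoring rule for repeat debridement and for PCD given for residual infection;
- one threshold, since the two sentences on IIIa differ.

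Keep the planned steps in the number-of-procedures outcome, and report a sensitivity analysis of the primary endpoint with all such steps counted. Preferably, have the grading done by assessors who do not know the allocation. Confirm that the 20% and 45% under Sample size use the same definition, and restate the power if they do not. This changes scoring only, not treatment.

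**Cost.** The wording and one extra analysis are cheap. The indication for each re-intervention must be recorded; the surgical data listed under Data collection do not name it. A rule that does not count repeat procedures could also hide genuine treatment failures, which is why the sensitivity analysis is needed. If the 45% included planned escalation, the expected difference and the power will be less favourable than stated.
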